## Abstract

Background: Borderline Personality Disorder (BPD) is a debilitating mental health condition characterized by emotional dysregulation and interpersonal dysfunction, with perceived social rejection exacerbating these issues. Emerging evidence suggests that a single session of transcranial direct current stimulation (tDCS) over the right ventrolateral prefrontal cortex (rVLPFC) may decrease the unique tendency of BPD patients to feel rejected even when socially included during a laboratory task. Objectives: This protocol outlines a double-blind, sham-controlled study evaluating the longitudinal effects of repeated anodal tDCS over the right ventrolateral prefrontal cortex (rVLPFC) on rejection-related emotions (RRE) during real-life social interactions in individuals with BPD. Methods: Sixty BPD patients will be randomized to receive real or sham tDCS across 10 daily sessions, coupled with an ecological momentary assessment (EMA) protocol capturing emotional and behavioral responses to real-life social interactions over four timepoints: baseline, during treatment, ten days post-treatment, and three months post-treatment. Primary outcomes include changes in RRE, with exploratory analyses examining feelings of social connection, aggressive tendencies, trust toward others, and interpersonal and affective dynamics. Multilevel modeling will assess temporal and group-level effects. Expected Results and Impact: This study aims to establish the efficacy of tDCS in reducing BPD patients’ negative emotional response in real-life social situations and to determine whether such effects are maintained in time. The findings could advance the clinical application of tDCS as an adjunctive intervention to alleviate social–emotional impairments in BPD, addressing gaps in current treatment approaches and guiding future research into the neural mechanisms of social emotion regulation.

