Based on previous evidence that among HC anodal tDCS over the rVLPFC decreases aggressive reactions following social exclusion [20], and that BPD patients feel disconnected by others even in including and over-including scenarios [10] and exhibit extensive impairments in trust processes [27], the EMA protocol will also assess participants’ momentary feelings of social connection and trust toward others, their level of aggressive tendencies, and their perception of their own and their interaction partner’s behavior.

In our prior work, we showed the utility of EMA to evaluate affective and interpersonal changes in patients with BPD treated in psychotherapy, suggesting not only that the occurrence and volatility of daily negative affects decreased over time periods but also that this was accompanied by shifts in interpersonal perceptions [28]. BPD patients (N = 45) made simple ratings of their perceptions of interpersonal warmth/dominance (i.e., is the behavior friendly or unfriendly, agentic or passive?) and affect valence/arousal (i.e., is the emotion happy or sad, intense or quiet?) in both themself and others; multilevel models examined shifts in covariations between these dimensions over the time period during an intervention. Related to the present study, over the course of treatment, BPD patients’ momentary perceptions of others as being more affectively aroused and interpersonally dominant was increasingly connected to seeing them as more friendly. Put differently, the tendency to view an interpersonal event as warm and friendly was associated with a wider range of other’s behaviors and affects, now including even those perceived to be more emotionally intense and agentic. Thus, EMA provided a powerful tool for demonstrating whether experiences of warmth/closeness were associated with highly contextual versus broad interpersonal experiences, as well as shifts in those associations over time via intervention.

Our main hypothesis is that participants receiving the actual tDCS protocol will report decreased RREs over time periods during daily interpersonal interactions (significant change T0–T1, sustained in T2) than participants receiving the sham protocol. We will also explore whether this decrease is also sustained 3 months after the end of the tDCS protocol (T3).

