### 2.3. EMA Protocol

To measure the emotional and behavioral response stemming from participants’ everyday social relations, participants, after being trained on the use of an app on their smartphones, will undergo an EMA protocol in four different assessment periods, each lasting 10 days (Figure 2). The specific details are as follows:

T0: starting 10 days before the tDCS protocol to assess the baseline behavioral and emotional responses to social relations;

T1: during the 10 days of the tDCS protocol, in order to assess the effects of tDCS during the protocol;

T2: 10 days after the end of the tDCS protocol, to assess if the potential effects persist even after the end of the tDCS protocol.

T3: 12 weeks following the end of the tDCS protocol for 10 days, to assess if the potential effects persist in the long-term after the end of the tDCS protocol.

For each day of the EMA protocol, participants will receive five prompts from an app on their smartphones at five different times of the day: two in the morning (around 9 to 12.30 pm), two in the afternoon (around 15 to 19 pm), and lastly, one in the evening (around 20 to 22 pm), asking them to assess the last significant social encounter of the day (lasting at least 5 min). Moreover, participants will be asked to spontaneously report their reactions immediately after any significant social encounter (lasting at least 5 min) at least three times/day. The average EMA survey completion time in our prior study [28] was 2 min 43 s, or about 15 min per day.

For both signal-initiated and event-initiated EMAs, participants will be directed to an online survey that will ask respondents to fill in the following measures:

Primary Outcome Measure: Rejection-related emotions. Assessed by the Rejected Emotions Scale [46]. Participants will rate how they felt during *Cyberball* on a number of adjectives measuring six emotions: anger, happiness, hurt, rejection feelings, anxiety, and sadness. These ratings will be made on a 7-point scale ranging from “not at all” to “extremely”. For the sake of compliance and brevity, the original scale, assessing the different dimensions with 4 items each, has been shortened to a single item assessing the singular dimensions, for a total of 6 items.

Exploratory outcome measures:

Interpersonal and Affect Assessments.

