Patients will make event-contingent recordings following any interpersonal interaction lasting 5 min or longer. Ratings include their own interpersonal behavior (self-agency, self-communion) as well as their perception of their interaction partner’s interpersonal behavior (other-agency, other-communion). Higher scores indicate greater perceived dominance (from unassured–submissive to assured–dominant) and communion (from cold–quarrelsome to warm–agreeable). Patients will also rate their own affect (self-activation, self-valence) as well as their perception of their interaction partner’s affect (other-activation, other-valence). Higher scores indicate higher perceived activation (from quiet–passive to active–energized) and higher perceived valence (from sad–upset to happy–pleased).

Social connection. Assessed by the Inclusion of Other in the Self scale (IOS) [47], a single-item, pictorial measure of the psychological overlap between the self and the other. Higher scores indicate a higher degree of social connection. Participants will rate their impression of closeness with the other person during the interpersonal event by choosing among 7 images. Each image shows two diagrams, the former related to “yourself”, the latter related to “the other”, which can be completely separated (“A”) up to partially overlapped (“G”).

Trust will be assessed by asking the participants “In this social interaction, how much did you trust the other person?”. This measure will be scored on a 7-point scale ranging from “not at all” to “extremely”.

Aggressive temptations. Assessed by the Aggressive Temptation Scale—short version (ATS) [48], a 6-item questionnaire (1–7 Likert scale) measuring participants’ self-reported temptation to engage in aggressive behaviors (e.g., humiliating another person or ignoring another person). Particularly, participants will be reminded that this scale will not ask whether they would have performed each behavior, but rather the degree to which they would have been tempted to do each one during the interpersonal event they are rating.

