tDCS will be delivered during the *Cyberball* paradigm, a virtual ball-tossing game that reproduces different levels of social inclusion by manipulating the percentage of tosses that participants receive from two other computer-controlled co-players. After about five minutes of stimulation, participants will play first the social inclusion (33% of throws received), then the social exclusion (10% of throws), then the over-inclusion (45% of throws) conditions of the game. The order of these experimental phases is fixed, ensuring that the game ends with the over-inclusion condition, which is typically not associated with negative emotions in BPD [10,13], for ethical reasons. The choice in the study design to deliver tDCS during the *Cyberball* stimulation design is based on recent evidence on the state-dependency of tDCS, pointing to the opportunity to timelock the stimulation to a concurrent activity involving the stimulated target area in order to achieve specific effects [54,55,56]. tDCS experiments will be conducted by trained investigators and participants can stop the stimulation at any time if they want to. TDCS is not invasive, with few adverse effects, mostly consisting of an itching sensation during the ramp-in phase of the current [57]. At the end of the tDCS treatment, participants will complete a questionnaire to investigate the eventual side effects and to control for tDCS blinding effectiveness [58]. Checking blindness effectiveness indeed becomes more crucial when multiple sessions are included in a protocol. In particular, the questionnaire [58] explores participants’ beliefs on tDCS condition assignment. The frequency of correct vs. incorrect guesses will then be compared between the real vs. sham control group by means of a Chi-square test.

All subjects will be extensively debriefed upon completion of the study. They will receive detailed information about the tDCS protocol and its purpose and will have the opportunity to have their data deleted should they so wish.

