We expect that BPD patients undergoing the real tDCS protocol will show lower levels of RREs elicited by daily social interactions compared to sham controls and that this reduction in RRE will be sustained even 10 days after and up to 3 months after the end of the tDCS protocol. Consistently, we also expect that the tDCS protocol will improve BPD patients’ perception of their interactions as being increasingly warm, friendly, and inclusive over time periods across a wider range of daily experiences of inclusion, affective intensity, and interpersonal dominance, thus broadening their perception of interpersonal behaviors and affects. Specifically, participants in the real tDCS group are expected to rate their own and their interaction partners’ behaviors as being increasingly warm and affiliative, with a greater perception of friendliness and inclusion compared to the sham group. We also anticipate that affective responses during daily social interactions will shift over time, with participants in the real tDCS group reporting lower negative affect and higher positive affect during social encounters compared to the baseline and the sham condition.

Regarding trust, our hypothesis is that repeated tDCS, by reducing negative emotional responses to social interactions, could favor an increased sense of trust toward others, reflected in higher trust ratings during interpersonal interactions over time. Since BPD patients often perceive social interactions as unpredictable or threatening, we expect that tDCS will mitigate this tendency, leading to a more stable and positive perception of others’ intentions and behaviors.

Therefore, we expect that repeated sessions of tDCS over the rVLPFC will lead to enduring improvements in emotional and interpersonal regulation in daily life in BPD. Specifically, this will be reflected in lower rejection-related emotions, enhanced social connection, increased trust, and more positive affective and interpersonal experiences across a broad range of social encounters.

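### The primary EMA outcome is defined as feelings during Cyberball, which contradicts the trial's real-life endpoint and leaves the item with no referent at T0, T2 and T3

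*Protocol article*

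**What the plan says.** Section 2.3 (EMA Protocol) sets up a smartphone survey in four periods. At each prompt the participant is directed to a real encounter, the app "asking them to assess the last significant social encounter of the day (lasting at least 5 min"). Participants also report spontaneously after such encounters. For both kinds of report, "participants will be directed to an online survey that will ask respondents to fill in the following measures". The first measure on that list is the primary outcome, the Rejected Emotions Scale, described as follows: "Participants will rate how they felt during *Cyberball* on a number of adjectives measuring six emotions". The same paragraph cuts the scale to one item per emotion, six in all, to limit burden.

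The Abstract states that the study evaluates the effect of repeated stimulation "on rejection-related emotions (RRE) during real-life social interactions in individuals with BPD". The main hypothesis in the Introduction is that the actively stimulated participants "will report decreased RREs over time periods during daily interpersonal interactions". Section 3 expects that they "will show lower levels of RREs elicited by daily social interactions compared to sham controls".

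Section 2.4 says where the game belongs: "tDCS will be delivered during the *Cyberball* paradigm, a virtual ball-tossing game". It is described nowhere else in the study procedures.

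**The concern.** This is the only sentence in the article that says what the primary item asks participants to rate, and it names a laboratory game instead of a daily-life encounter. The question that sets this trial apart from the earlier laboratory work is whether the effect carries over to ordinary social contact. A Cyberball referent removes that element from the primary outcome.

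It also does not fit the schedule. The main hypothesis is a change from T0 to T1 that is sustained at T2. If the item can be answered only where the game is played, the T0 value does not exist and neither the change nor its maintenance is defined. If participants instead answer about the game in T1 and about something else in the other periods, the contrast mixes two referents. No analysis could later separate them.

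**Working it through.** **Step 1. What each part of the article refers to.**

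| Place in the protocol article | What is rated or targeted |
|---|---|
| Abstract, objective | Real-life interactions |
| Introduction, main hypothesis | Daily interactions |
| Section 2.3, survey prompt | Most recent qualifying real encounter |
| Section 2.3, Rejected Emotions Scale (primary) | **Cyberball** |
| Section 2.3, trust item: "In this social interaction, how much did you trust the other person" | The interaction being reported |
| Section 2.3, closeness scale | The interpersonal event |
| Section 2.3, aggressive temptation scale | The interpersonal event being rated |
| Section 3, expected result | Daily interactions |

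Only the primary item points to the game.

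**Step 2. When Cyberball is available to be rated.** Section 2.4 places it within the stimulation sessions, given daily for 10 working days. Section 2.3 aligns T1 with those sessions, starts T0 before them, and places T2 and T3 after they have ended. At T0 the participant has, on the documents, not yet played. At T2 and T3 no session takes place and only a memory of past ones is left.

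**Step 3. How many planned reports this covers.** Inputs from Section 2.1: 5 prompts per day, 10 days per period, 80% compliance, three periods for T0–T2, and a further 40 observations at T3 for the participants who agree to follow-up.

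- Prompts per period: 5 × 10 = 50. Over T0–T2: 3 × 50 = 150, which is the article's own figure.
- Expected reports per period: 50 × 0.80 = 40. Over T0–T2: 3 × 40 = 120, again the article's figure.
- Reports in T1, the only period with Cyberball: 40.
- Reports in T0 and T2, with no game to rate: 120 − 40 = 80, and 80/120 = 67%.
- For a participant who also completes T3: (80 + 40)/(120 + 40) = 120/160 = 75%.

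These counts cover prompted reports only. Section 2.3 also asks for at least three spontaneous reports per day through the same survey, so they are not a total of all primary-outcome records.

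**Step 4. Whether the wording works within T1.** There are at most 10 sessions against 50 prompts, so most prompts do not follow a new session. Each session also runs inclusion, exclusion and over-inclusion phases in turn (Section 2.4), and the sentence does not say which is meant. The literal reading is therefore unclear even in the one period where the game is played.

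**The case against.** The strongest reply is that the intent is not in real doubt. Section 2.3 opens by saying that the survey measures responses to everyday social relations, its prompts concern real encounters, and the literal reading defeats itself in three of four periods. The sentence looks like text carried over from the laboratory study. It is a description in an article and not a quoted question, unlike the trust item, which is given verbatim. The app text is not shown. Most of this stands: nothing indicates a decision to have patients rate the game from home, and the carry-over explanation is plausible, though it is an inference.

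What does not follow is that the sentence can be left alone. It is a positive statement in the primary outcome definition, so neither the condensed format of an article nor an unseen analysis plan explains it. It also cannot be read as a separate rating made during the stimulation sessions, because it sits in the list of survey measures and the scale was shortened for compliance with that survey.

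A reader might go further and infer that every primary-outcome record is compromised, or that the trial would in effect repeat the laboratory result. The article supports neither. The first requires knowing what the app displays. The second ignores that the laboratory study was a single session comparing game conditions; a misworded survey answered several times a day after real encounters would not reproduce that design. How the six ratings are combined into a score is a separate matter that an article may leave to the full protocol, and it is not part of this point.

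**Conclusion.** The contradiction is certain on the text: the primary outcome definition in Section 2.3 conflicts with the prompt in the same section, the objective, the hypothesis, the expected result and the sibling items, and no other part of the article resolves it. Followed as written, the item has no referent for 80 of 120 expected prompted reports per participant over T0–T2 and for all of T3, and the T0–T1 change in real-life rejection-related emotions could not be estimated. This rests on Cyberball being played only in the stimulation sessions, as the article describes, and on its 80% compliance assumption for the counts; the contradiction itself depends on no number.

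Harm to the data is not shown. It is conditional on the deployed question carrying the Cyberball wording. Sample size and power are unaffected. The correction is nevertheless required, because the sentence is the only statement of what the primary endpoint measures.

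**What to change.** Reword the sentence in Section 2.3 so that participants rate how they felt during the social interaction they are reporting, with the same stem at T0, T1, T2 and T3 and for both prompted and spontaneous reports. Check that the app and the material used to train participants carry that stem. Section 2.1 partly uses the past tense for enrolment and event ratings, which leaves open whether collection has begun. If any reports were collected under the Cyberball wording, state how many, in which periods and in which arm.

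The cost is one sentence in the protocol and a check of one question stem. No change to the design, sample size or schedule is needed.

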### 2.4. Transcranial Direct Current Stimulation (tDCS) Protocol

Participants will be randomly assigned to two stimulation conditions: anodal (real) or sham tDCS over the rVLPFC. The tDCS treatment, either real or sham, will last 10 working days and comprise 20 min daily sessions. The stimulation will be applied at an intensity of 1.5 mA, with electrodes of 25 cm^2^ (anode, current density of 0.06 mA/cm^2^) and 35 cm^2^ (cathode, current density 0.042 mA/cm^2^) in line with the safety standards of tDCS [24]. We opt for differently sized electrodes to increase the focality of the stimulation [24]. In the sham modality, all the stimulation parameters (electrode sizes and montage, current intensity, number of sessions) will be kept identical, except for the stimulation duration, which will last only 20 s, with 30 s of rump-in/out as in the real condition to maintain the same physical sensations, thus keeping the participants blind to the tDCS condition [24,49]. An intracephalic montage will be adopted, with the anode placed over the rVLPFC, while the cathode will be placed on the contralateral supraorbital region.

We opt for an intracephalic montage based on prior research on tDCS clinical use [50,51], and to maintain consistency with the montage and tDCS parameters that effectively reduced pain-related emotions in our previous work [19,20,52]. The same electrode positioning procedure, based in the EEG 10-20 system of our previous studies [19,20,52], will be employed. Specifically, the anode will be positioned over F6 (MNI coordinates: 58, 30, 8), which corresponds to the rVLPFC. The effectiveness of such a montage to target the rVLPFC has been tested employing the free software COMETS v.1.04 (http://www.COMETStool.com, accessed on 15 March 2025) [53] to run a computational model of the current flow (figure below taken from Riva et al., 2017 [52]). This model showed that the strongest electric field was concentrated around the cortical area beneath the target electrode (Figure 3).

The tDCS device (DC-STIMULATOR, NeuroConn GmbH, Ilmenau, Germany) includes a study mode for a double-blind procedure. Namely, a numeric code (four digits), corresponding to either anodal or sham tDCS, will start the stimulation, thus preventing the awareness of the stimulation condition in both participants and the research assistant—neither of whom is aware of the correspondence between the code and the type of stimulation that will be delivered. More specifically, the research assistant will read on participants’ log files one of two codes for each new participant. Unbeknownst to the research assistant who delivers the tDCS, two codes will trigger anodal tDCS, the other two will trigger sham stimulation. Thus, the proposed study will be a double-blind study, meaning that both patients and investigators involved in the tDCS sessions will be blinded to the stimulation conditions (real or sham tDCS). Before starting the experiment, an investigator different from the one who will apply the tDCS stimulation will set the tDCS parameters for real and sham stimulation by using two different numerical codes. Such codes will be saved in an unmodified mode in the tDCS device so that at the beginning of each session, according to the randomization, active or sham stimulation will be chosen by only considering their corresponding codes. The unmodified mode rules out the possibility that codes and stimulation parameters will be changed during the experiment. To further check for participants blindness, at the end of the treatment, a questionnaire inquiring about the participant’s guess on the real vs. sham condition assignment and eventual side effects of the stimulation will be administered.

tDCS will be delivered during the *Cyberball* paradigm, a virtual ball-tossing game that reproduces different levels of social inclusion by manipulating the percentage of tosses that participants receive from two other computer-controlled co-players. After about five minutes of stimulation, participants will play first the social inclusion (33% of throws received), then the social exclusion (10% of throws), then the over-inclusion (45% of throws) conditions of the game. The order of these experimental phases is fixed, ensuring that the game ends with the over-inclusion condition, which is typically not associated with negative emotions in BPD [10,13], for ethical reasons. The choice in the study design to deliver tDCS during the *Cyberball* stimulation design is based on recent evidence on the state-dependency of tDCS, pointing to the opportunity to timelock the stimulation to a concurrent activity involving the stimulated target area in order to achieve specific effects [54,55,56]. tDCS experiments will be conducted by trained investigators and participants can stop the stimulation at any time if they want to. TDCS is not invasive, with few adverse effects, mostly consisting of an itching sensation during the ramp-in phase of the current [57]. At the end of the tDCS treatment, participants will complete a questionnaire to investigate the eventual side effects and to control for tDCS blinding effectiveness [58]. Checking blindness effectiveness indeed becomes more crucial when multiple sessions are included in a protocol. In particular, the questionnaire [58] explores participants’ beliefs on tDCS condition assignment. The frequency of correct vs. incorrect guesses will then be compared between the real vs. sham control group by means of a Chi-square test.

All subjects will be extensively debriefed upon completion of the study. They will receive detailed information about the tDCS protocol and its purpose and will have the opportunity to have their data deleted should they so wish.

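### The only side-effect questionnaire described comes once, at the end of a ten-session course, so it relies on recall and nothing ensures that patients who stop early complete it

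*Protocol article*

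**What the plan says.** Everything relevant is in Section 2.4 of the protocol article.

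- **Length of the course:** "The tDCS treatment, either real or sham, will last 10 working days and comprise 20 min daily sessions".
- **Timing of side-effect collection:** this is given twice. The paragraph on blinding places "at the end of the treatment, a questionnaire inquiring about the participant’s guess on the real vs. sham condition assignment and eventual side effects". The paragraph on Cyberball repeats it: "At the end of the tDCS treatment, participants will complete a questionnaire to investigate the eventual side effects".
- **Expected effects:** "TDCS is not invasive, with few adverse effects, mostly consisting of an itching sensation during the ramp-in phase of the current". Sham keeps the same 30 s ramp as real stimulation so that the physical sensations match.
- **Early stopping:** "participants can stop the stimulation at any time if they want to". No stopping rate is given, and the article does not say whether or when someone who stops completes the questionnaire.
- **Planned analysis of the questionnaire:** "The frequency of correct vs. incorrect guesses will then be compared between the real vs. sham control group by means of a Chi-square test". No analysis of the side-effect answers is stated.

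**The concern.** The timing suits the allocation guess but not the side effects. A guess is sensibly asked once, when the course is over. A sensation that lasts for the ramp and can come back at each of ten sessions is poorly captured by one retrospective question about the whole course. Some brief effects will be forgotten, and the answer cannot show at which sessions they occurred.

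The timing is also tied to reaching the end of treatment, while participants are free to stop. A patient who ends the course because of a side effect is the one whose report matters most, and nothing in the text triggers the questionnaire at that point. If such patients are missed, side-effect reports go missing because of side effects. Their allocation guesses go missing too, although Section 2.4 itself says the blinding check matters more when there are several sessions.

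What is at stake is the completeness of the side-effect record and of the blinding check. The analysis of rejection-related emotions does not depend on this questionnaire.

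**Working it through.** The plan states no figure on this point, so there is none to reproduce. The check is a reading of the text, a simple count, and an illustration under assumed rates.

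**Step 1: where the questionnaire falls.** Treatment lasts ten working days of daily sessions, and the questionnaire comes at the end of treatment. For a patient who completes the course, that is after session 10.

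**Step 2: recall interval.** Ten working days starting on a Monday run to the Friday of the next week: 5 + 2 + 5 = 12 calendar days. Starting on any other weekday, the course crosses two weekends: 10 + 4 = 14 calendar days. From the first session to the last, 11 to 13 days elapse, so a first-session sensation is recalled at that distance.

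**Step 3: records against exposures.** 60 patients × 10 sessions = 600 planned sessions, with at most 60 questionnaires, or one per ten sessions. This does not mean that 90% of exposures go unrecorded, since one questionnaire can ask about the whole course. It does mean that there is no information by session.

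**Step 4: what early stopping could do.** Assumptions that are not in the document: 30 patients in an arm (the allocation ratio for the 60 is not stated), every stopper has a side effect, every stopper misses the questionnaire, and completers recall perfectly. With *n* = 30, *a* truly affected and *s* stoppers:

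- true rate = *a* / *n*
- rate among those who complete the questionnaire = (*a* − *s*) / (*n* − *s*)

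| Truly affected | 1 stopper | 3 stoppers | 5 stoppers |
|---|---|---|---|
| 6/30 = 20.0% | 5/29 = 17.2% | 3/27 = 11.1% | 1/25 = 4.0% |
| 10/30 = 33.3% | 9/29 = 31.0% | 7/27 = 25.9% | 5/25 = 20.0% |
| 15/30 = 50.0% | 14/29 = 48.3% | 12/27 = 44.4% | 10/25 = 40.0% |

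The understatement is about 2 to 3 percentage points with one stopper (50.0 − 48.3 = 1.7; 20.0 − 17.2 = 2.8). It is 10 to 16 points with five (50.0 − 40.0 = 10.0; 20.0 − 4.0 = 16.0). If stoppers complete the questionnaire when they stop, it is zero. Imperfect recall among completers would come on top and cannot be quantified from the document.

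**Step 5: blinding check.** Each stopper who is missed removes one guess from the Chi-square test. With three missed per arm, for example, 60 − 6 = 54 guesses remain.

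**The case against.** Several points on the other side carry weight.

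- **A reader might infer that early stoppers never reach the questionnaire.** The text does not say so. The end of treatment can be read as the point at which a given patient's treatment ends, and stopping a stimulation is not the same as leaving the study. The document is silent here and does not exclude these patients. This stands, although the ten-working-day definition makes the later time point the more natural reading.
- **A reader might infer that a tolerability comparison between arms is biased.** None is planned. The only test on this questionnaire concerns guesses, and the objectives in Section 3 do not include safety. The statement in the Introduction that tDCS is safe and well tolerated rests on cited work and is not a claim this trial sets out to prove. This stands.
- **A reader might infer that more reports are lost in the real arm, because current flows for 20 min rather than 20 s.** For the effect the article names, exposure is matched by design: sham has the same ramp, in order to give the same sensations. Nothing in the document shows differential loss. This stands.
- **Session-level recording of adverse events may be in the full protocol, and trained staff are present at every session.** Both are fair. An article need not list every procedure, and staffed daily contact offers informal chances to notice a problem. But the article is not merely silent: it states twice when the side-effect questionnaire is given, and that stated timing is what fits poorly.
- **Asking about sensations ten times may itself prompt guessing.** This is a real cost and belongs with the fix.

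**Conclusion.** The point holds in a limited form. The timing stated for the side-effect questionnaire makes the data depend on recall over about two weeks, and that weakness is present even if nobody stops early. Nothing in the text ensures that a patient who stops early completes the questionnaire. Side effects may therefore be under-recorded, and some allocation guesses may be lost from the blinding check.

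The size cannot be computed, because the document gives neither a stopping rate nor a side-effect rate. The illustration runs from zero (stoppers assessed when they stop) to about 16 points (five of 30 stop, all affected and all missed), and it rests entirely on the stated assumptions. With the few adverse effects the article expects, the lower end is more plausible. No difference between arms follows from the document. The primary outcome is unaffected. This is a cheap improvement to data capture and does not threaten the trial's main conclusion.

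**What to change.** In Section 2.4, separate the two parts of the questionnaire:

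1. Give the existing side-effect items briefly after each session, and on the day a patient stops a session or the course early.
2. Ask the allocation guess only once, at the end of the course or at early stop, so that stoppers stay in the blinding check.
3. Report side effects descriptively by arm, per session and per patient, over all randomised patients who started stimulation. Early stoppers stay in the denominator.

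If the full protocol already provides for this, one sentence in the article saying so is enough.

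**Cost:** one or two minutes per session at visits that already take place, with no new instrument. Repeated questions may slightly raise symptom reporting or prompt patients to guess their allocation, and it should not be taken for granted that this would be equal in both arms. Keeping the items short, wording them identically in both arms and leaving the guess to the end limits that risk.
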